**Methods:**

The dose-escalated hypoxia-adjusted radiotherapy trial is an open-label, parallel, randomised, single-centre, phase II study. Patients with HNC will undergo [18F]. FMISO PET CT to identify hypoxic regions. Normoxic patients will be labeled as Arm 1 and will not be part of the primary assessment. Patients with hypoxia will be stratified into two arms (2 and 3). Arm 2 will receive standard radiotherapy of 70 Gy in 2 Gy fractions, while Arm 3 will receive an additional boost to the hypoxic sub-volumes, delivering a total of 80 Gy (Phase 2). All patients in Arms 2 and 3 will also receive concurrent chemotherapy with cisplatin. Patients will be monitored weekly for treatment tolerance, with acute adverse events recorded according to National Cancer Institute Common Terminology Criteria for Adverse Events v5.0. The primary endpoint is LRC, defined as the time from randomisation to the first histopathologically confirmed relapse of locoregional disease. Secondary endpoints include OS, locoregional relapse-free survival, acute and late toxicity and patient-reported outcomes assessed using the European Organisation for Research and Treatment of Cancer QLQ-C30 and QLQ-H&N35 questionnaires.

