## Adherence to protocol and concomitant care

Patients will be monitored weekly to assess their tolerance to treatment. Any patient exhibiting grade 3 or higher toxicity will require urgent therapeutic intervention. The most anticipated side effects are mucositis and dysphagia. Patients will be evaluated weekly for the need for nutritional support and feeding tube placement, as well as on an as-needed basis. In rare instances of severe toxicities not responding to conservative measures, a treatment break may be necessary. The resumption of radiotherapy will be contingent upon the resolution of major toxicities, with the aim of restarting radiotherapy as soon as clinically feasible.

Outcome measures: Oncological outcomes will be collected by a designated team of head and neck specialists (radiation oncologist, surgeon and radiologist)

Response assessment*:* The patients would be assessed for the first time after 12 weeks of completion of definitive radiotherapy. The patients would be assessed by 18-FDG PET CT (± MRI) and direct laryngoscopy. The need for biopsy versus repeat imaging at a short interval will be taken by a multispeciality clinic taken into view the clinical examination, laryngoscopy findings (including narrow band imaging) and radiological findings.

*Primary endpoint: locoregional control* (LRC): LRC is defined as the absence of tumour recurrence or progression within the primary tumour site and the regional lymph nodes, as determined by clinical evaluation, imaging studies and/or biopsy confirmation. LRC will be assessed at predefined time points, with the primary time point being 2 years post-treatment. Locoregional recurrence within 2 years post-treatment is associated with significant morbidity and reduced quality of life. Therefore, 2-year LRC serves as a clinically meaningful endpoint to guide treatment decisions and optimise outcomes for patients receiving escalated radiation doses.

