### Secondary endpoints

*Overall Survival (OS)*: The duration of OS is defined as the time from the date of randomisation to death from any cause. If there is no death, the OS duration will be censored at the time of analysis.

*Locoregional relapse-free survival (LRFS)*: LRFS is defined as the time from the date of randomisation to the first histopathologically confirmed relapse of locoregional disease. If there is no confirmed recurrence, the LRC duration will be censored at the time of analysis. Death from any cause will be considered as an event in LRFS.

*Acute toxicity:* Acute adverse events will be assessed and recorded according to the NCI CTCAE version 5.0 [40]. Evaluations will be conducted at baseline, mid-treatment (week 4), immediately post-treatment, 2 weeks post-radiotherapy and subsequently at 3 months post-treatment.

*Late toxicity assessment*: Long-term toxicities of the upper aerodigestive tract will be recorded at 1 and 2-year follow-ups. They will be assessed using the RTOG long-term toxicity assessment [41].

*Patient-reported outcome*: The data will be collected by the trial coordinator and, research nurse by collecting proformas filled by patients.

European Organisation for Research and Treatment of Cancer (EORTC) head and neck questionnaires: The Hindi versions of the EORTC QLQ-C30 [42] and QLQ-H and N35 questionnaires [43, 44] will be obtained from the QoL unit, EORTC Data Centre in Brussels, Belgium. The EORTC QLQ-C30 questionnaire consists of five functional scales that include physical, role, cognitive, emotional and social; three symptom scales that include fatigue, pain and nausea/vomiting; a global QoL scale; and six single items that include dyspnea, insomnia, appetite loss, constipation, diarrhoea and financial difficulties. The QLQ-H and N 35 questionnaires consisted of seven multiple-item scales that assess the symptoms of pain, swallowing ability, senses (taste/smell), speech, social eating, social contact and sexuality and six single-item scales that assess the presence of symptomatic problems associated with teeth, mouth opening, dry mouth (xerostomia), sticky saliva, coughing and feeling ill. All the scales of the EORTC QLQ-C30, QLQ-H and N35 range from 0 to 100.

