### Data collection and analysis

All data will be collected in the central registry of the institute and anonymised. All statistical analyses were performed using the Statistical Package for Social Science System (SPSS v26, SPSS Inc, Chicago, IL) or equivalent software. Continuous variables will be written as mean (along with standard deviation) and median (along with interquartile range). Categorical variables will be represented as frequencies and percentages. Inter-cohort testing will be performed using chi-square for categorical variables and independent-t/nonparametric tests for continuous variables. Time-to-event endpoints will be measured from the date of randomisation to the date of failure or last follow-up. The LRC rate at 2 years will be estimated using the Kaplan–Meier method, with the time to locoregional failure defined as the duration from the start of radiation therapy to the first documented recurrence or progression within the primary tumour site or regional lymph nodes. The LRFS and OS, as mentioned earlier, death from any cause will be considered a failure. The LRFS and the OS rates will be estimated using the Kaplan–Meier product-limit method for each arm. Their distributions will be compared between treatment arms (Arms 2 and 3) with a two-sided log-rank test ≤ 0.05. The clinicopathological characteristics, survival outcomes and treatment modalities will be analysed using the univariate and multivariate Cox proportional hazards model. All eligible patients will be included in the analysis in the arm to which they were randomly assigned (intent-to-treat).

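### The primary endpoint, locoregional control, is given two event rules and two starting clocks that cannot all apply

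*Protocol article*

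**What the plan says.** Five places in the protocol article bear on locoregional control (LRC) or on its companion endpoint, LRFS.

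- **Abstract, Methods:** "The primary endpoint is LRC, defined as the time from randomisation to the first histopathologically confirmed relapse of locoregional disease".
- **Adherence to protocol and concomitant care, primary endpoint paragraph:** LRC is absence of recurrence or progression "as determined by clinical evaluation, imaging studies and/or biopsy confirmation", "with the primary time point being 2 years post-treatment". The response-assessment paragraph just above it says "The need for biopsy versus repeat imaging at a short interval will be taken by a multispeciality clinic".
- **Data collection and analysis, general rule:** "Time-to-event endpoints will be measured from the date of randomisation to the date of failure or last follow-up".
- **Same section, next sentence:** the 2-year LRC rate is a Kaplan-Meier estimate "with the time to locoregional failure defined as the duration from the start of radiation therapy to the first documented recurrence or progression". The section closes with "All eligible patients will be included in the analysis in the arm to which they were randomly assigned (intent-to-treat".
- **Secondary endpoints:** "LRFS is defined as the time from the date of randomisation to the first histopathologically confirmed relapse of locoregional disease". Death from any cause also counts as an LRFS event.

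The article does not say which definition prevails.

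**The concern.** LRC is the only primary endpoint, and two analysts following different sections would count different events from different days.

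**Event rule.** The abstract recognises a failure only when histology confirms it. The other two LRC definitions do not need histology. Since the clinic chooses between biopsy and repeat imaging, failures without biopsy are foreseeable. The trial is open-label, so a discretionary biopsy could decide whether an event exists, and if biopsy is used differently in the two arms the comparison itself is biased.

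**Clock.** A clock that starts with radiotherapy has no time zero for a patient who is randomised but never irradiated, yet the analysis is by intention to treat.

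**Coherence with LRFS.** LRFS requires histology. A failure called on imaging alone is an LRC failure under the body of the article but not an LRFS event, so LRFS, which should include every LRC failure plus deaths, can look better than LRC.

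**Working it through.** **Inputs.** Rates of 59% and 84%, α = 0.05, 80% power and 62 per arm come from Sample size. Radiotherapy of 5 + 2 = 7 weeks comes from the Arm 2 section. Visits at 3, 6, 12, 18 and 24 months after radiotherapy come from Table 1. A two-sided test is taken from the log-rank statement for LRFS and OS, because Sample size does not state sidedness.

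**The plan's own figure.** With the pooled two-proportion formula, mean rate 0.715:

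n = [1.96·√(2·0.715·0.285) + 0.842·√(0.59·0.41 + 0.84·0.16)]² / 0.25² = 50 per arm, or 58 with continuity correction.

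The stated 62 is not reproduced from the stated inputs. That is a separate matter; 62 is used below as planned.

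**Power at 62 per arm with every failure counted.** Power = Φ[(d − 1.96·se₀)/se₁].

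- se₀ = √(2·0.715·0.285/62) = 0.0811
- se₁ = √[(0.2419 + 0.1344)/62] = 0.0779
- (0.25 − 1.96·0.0811)/0.0779 = 1.17, so power is 87.9%.

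**Event rule.** Suppose a fraction f of failures in each arm is never biopsied (an assumption, ranged over 10-30%). The histology-only rate is 1 − (1 − f)·0.41 in control and 1 − (1 − f)·0.16 in the experimental arm.

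| f | Control | Experimental | Difference (points) | Power at 62 per arm |
|---|---|---|---|---|
| 0 | 59.0% | 84.0% | 25.0 | 87.9% |
| 10% | 63.1% | 85.6% | 22.5 | 82.7% |
| 20% | 67.2% | 87.2% | 20.0 | 76.3% |
| 30% | 71.3% | 88.8% | 17.5 | 68.8% |

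**Clock, failures dated when they occur.** Assume a constant hazard from the start of radiotherapy and take 59% and 84% as the rates 24 months from that start. Then h = −ln(0.59)/24 = 0.02198 and −ln(0.84)/24 = 0.00726 per month. Seven weeks is 49/30.44 = 1.61 months. The interval from randomisation to radiotherapy is not stated; 0.5-1.5 months is assumed.

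| 24 months counted from | Months of hazard | Control | Experimental |
|---|---|---|---|
| Randomisation | 23.5 to 22.5 | 59.7-61.0% | 84.3-84.9% |
| Start of radiotherapy | 24 | 59.0% | 84.0% |
| End of treatment | 25.61 | 56.9% | 83.0% |

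Against the post-treatment reading, the control rate shifts by about 2-4 points and the experimental rate by about 1-2. The arm difference stays at about 24-26 points.

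**Clock, upper bound.** Suppose every failure is found only at a scheduled visit. The 24-month post-radiotherapy visit falls 24 + 1.61 = 25.6 months after radiotherapy starts, outside a 24-month estimate, so the last visit counted is at 18 + 1.61 = 19.61 months. The rates read exp(−19.61h) = 65.0% v 86.7% (21.7 points, power 81.5%), against 56.9% v 83.0% (26.1 points, power 89.6%) when read 2 years after treatment.

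**The case against.** **The clocks may be less opposed than they look.** The post-treatment wording sets a landmark, not a time origin, so a reader who infers three rival origins goes too far: there are two stated origins and one landmark. The analysis section could also be read as a general rule followed by a specific one for LRC. The abstract's wording nearly repeats the LRFS definition, so a mislabelled sentence is a plausible cause. All of this stands. It explains how the conflict may have arisen without removing it, because the specific rule still contradicts the abstract and still leaves never-irradiated patients without a time zero. The article does not say how many such patients to expect.

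**The clock barely affects the comparison.** It applies to both arms alike. A reader might take 65% v 87% against 57% v 83% as the expected effect, but that needs all detection to happen at scheduled visits, while the article provides for clinical evaluation and short-interval repeat imaging. It is an upper bound, and even then power stays above the planned 80%. This objection stands for the clock but not for the event rule.

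**The full protocol or a SAP may settle it.** Either may exist, so a reader should not infer that the definition will be picked after the data are seen; that is a risk, not an established fact. Conflicting statements about the primary endpoint are nonetheless more than detail left to another document.

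**Persistent disease.** A reader might infer that tumour that never clears would be counted as controlled. The article does not address it expressly, but that is an omission the full protocol or SAP may fill, not a contradiction, and it is not part of this point.

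**Conclusion.** The primary endpoint is wrong as written: two event rules that cannot be merged, two origins in consecutive sentences, and a landmark tied to neither origin. The event rule is the more serious part. Its size rests on an assumed 10-30% of failures unbiopsied, equal in both arms; power at 62 per arm then falls to between 83% and 69%, below the planned 80% at 20% unbiopsied or more. The clock is the smaller part, chiefly affecting the reported 2-year rates under a constant hazard and an assumed interval from randomisation to radiotherapy. The contradiction itself depends on none of these assumptions.

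**What to change.** Use one definition in the abstract, the primary endpoint paragraph, Secondary endpoints, and Data collection and analysis:

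- **Clock:** time from randomisation, for all randomised patients in the hypoxic arms, which fits the intention-to-treat rule.
- **Event:** first locoregional recurrence or progression under the clinical, imaging and/or biopsy rule already in the primary endpoint paragraph.
- **LRFS:** the same event rule plus death, so that every LRC failure is also an LRFS event.
- **Landmark:** a single 2-year reading on the randomisation clock. State openly that a failure first found at the 24-month post-radiotherapy visit falls after 24 months from randomisation and so is not in that estimate. Moving the landmark to a later month to capture that visit is not required: it would replace the stated 2-year endpoint and would depend on a randomisation-to-radiotherapy interval that the article does not give.

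The cost is a wording amendment, reported to the IRB and the funding agency as the ethics section requires, with no new visits or data. Some events will lack histological proof, and reported LRC will be lower than under the histology-only rule: in control by 4.1 points (63.1 − 59.0) if 10% of failures are unbiopsied, and by 12.3 (71.3 − 59.0) if 30% are.

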## Study/Trial design

DE-HyART is an open-label, parallel, randomised, single-centre, phase II study designed to evaluate the effectiveness and feasibility of dose escalation using FMISO PET scans for HNC. This superiority trial aims to assess the impact of integrating IMRT with simultaneous integrated boost (SIB) and dose escalation to hypoxic sub-volumes, as delineated by [18-F] FMISO, compared to standard-dose radiotherapy. The treatment protocol also incorporates concurrent chemotherapy with standard dosing of the physician’s choice and patients’ fitness. The protocol has been developed in accordance with SPIRIT guidelines [34, 35].

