### Participant screening, recruitment and consent [18F] FMISO PET CT and hypoxia identification

All eligible patients will be subjected to screening [18F] FMISO scan, labelled as baseline FMISO. The primary challenge with using FMISO is its lipophilic nature, which slows its clearance from normal tissues such as blood and muscle, resulting in a low signal-to-background ratio. Numerous studies [12, 36–39] have evaluated FMISO parameters with clinical endpoints, demonstrating that a TMR ranging from 1.2 to 1.6 significantly correlates with the reduction of hypoxic volumes during the course of radiotherapy.

Therefore, a TMR of 1.4 will be employed to differentiate hypoxic from normoxic patients (TMR ≥ 1.4 and < 1.4 will be labelled as hypoxic and normoxic, respectively). Standardised assessment of SUVmax and SUVmean will be utilised. Tumour SUVmax will be determined by generating a region of interest (ROI) of 1 cm^2^ at the most metabolically active region of the tumour. For background reference, the contralateral sternocleidomastoid muscle at the caudal edge of the hyoid bone will be used, with a similar ROI to calculate the TMR.

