### Timing of [18F] FMISO PET CT

All enrolled patients will undergo an [18F] FMISO PET CT scan. Patients exhibiting hypoxia, as determined by the PET results, will be randomised into either Arm 2 or Arm 3. A second [18F] FMISO PET CT scan will be performed between the fourth and fifth weeks of radiation therapy to evaluate the temporal variability of HSV.

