Age: 18–70 years Willingness to sign informed consent (written/video documentation) Performance status: ECOG 0 – 2 Histology proved – squamous cell carcinoma Any grade, gender Tumour sites: Oropharynx, Hypopharynx and Larynx Sufficient bone marrow reserve within the last 14 days. Hb: > 10 g/dl (corrected) TLC: > 4,000 per cumm Platelet: >1.5 Lakhs per cumm Liver functions and kidney functions within normal limits Nutritional and dental assessment before inclusion into the study	HPV (p16) positive tumours Prior surgery and/or radiation therapy given for any HNC T1/T2 Glottis Metastatic disease or disease not amenable for definitive locoregional treatment. Medical co-morbidity hampering the administration of radiation and/or chemotherapy Pregnancy or lactation

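### The analysis set is called intention-to-treat but is defined as eligible patients, not all randomised patients, which leaves room for exclusions after open-label allocation

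*Protocol article*

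**What the plan says.** The analysis set is stated once, at the end of the Data collection and analysis section of the protocol article: "All eligible patients will be included in the analysis in the arm to which they were randomly assigned (intent-to-treat". No other section shown says that all randomised patients will be analysed.

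Four other places bear on how to read it:

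- **Study/Trial design.** The trial is an "open-label, parallel, randomised, single-centre, phase II study".
- **Participant screening.** The word 'eligible' is used here for status before allocation: "All eligible patients will be subjected to screening [18F] FMISO scan, labelled as baseline FMISO".
- **Timing of [18F] FMISO PET CT.** Randomisation follows the scan: "Patients exhibiting hypoxia, as determined by the PET results, will be randomised into either Arm 2 or Arm 3".
- **Table 2.** Some criteria are baseline facts, such as "HPV (p16) positive tumours". Others call for judgement, such as "Medical co-morbidity hampering the administration of radiation and/or chemotherapy", or disease not suited to definitive locoregional treatment.

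**The concern.** The label and the rule do not match. An analyst who follows the label keeps every randomised patient. An analyst who follows the rule may leave out a patient found ineligible after allocation. Both could claim to have followed the protocol.

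This matters because allocation is open. The document does not say who would decide eligibility after randomisation, on what data, or without knowledge of the arm. Outcomes are gathered by specialists ("Oncological outcomes will be collected by a designated team of head and neck specialists"), and no blinding of that team is stated. The judgement-based criteria are the plausible route. A patient who cannot complete chemoradiation could be re-read as having had a disqualifying co-morbidity, and early progression could be re-read as disease that was never suited to definitive treatment. If that happened more in one arm, and more among failures, the comparison of Arms 2 and 3 on locoregional control, locoregional relapse-free survival and overall survival would no longer rest fully on randomisation. The Interim analyses section gives the avoidance of false positives as a reason for having no interim look, so closing this route fits the trial's own aim.

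**Working it through.** **The plan's own figure.** The document gives no number or rate for post-randomisation exclusions, so there is nothing to reproduce on this point. The inputs below come from the Sample size section and serve only to scale the risk: 62 patients per arm (62 + 62 = 124), control rate 59%, treatment rate 84%, α = 0.05. That section does not state sidedness. Two-sided is used here, as stated for the log-rank comparisons of the other time-to-event endpoints.

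**Step 1: selective loss with no true effect (assumed worst case).** Assume true control p = 0.59 in both arms, and that k patients are removed from Arm 3 only, all of them failures.

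- Apparent Arm 3 rate = 62 × 0.59 / (62 − k) = 36.58 / (62 − k)
- Shift d = apparent rate − 0.59
- SE = √[0.59 × 0.41 × (1/62 + 1/(62 − k))]
- False-positive rate = 1 − Φ(1.96 − d/SE) + Φ(−1.96 − d/SE)

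| k dropped | Apparent Arm 3 rate | d | False-positive rate |
|---|---|---|---|
| 0 | 59.0% | 0 | 5.0% |
| 1 | 60.0% | 0.010 | 5.1% |
| 3 | 62.0% | 0.030 | 6.3% |
| 6 | 65.3% | 0.063 | 10.7% |

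For k = 3: SE = √[0.2419 × (1/62 + 1/59)] = 0.0894 and d/SE = 0.335. The two tails are about 0.052 and 0.011, which sum to 0.063.

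For k = 6: SE = √[0.2419 × (1/62 + 1/56)] = 0.0907 and d/SE = 0.697. The tails are about 0.103 and 0.004, which sum to 0.107.

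To judge how extreme this is: expected Arm 3 failures are 62 × 0.41 = 25.4, so 3 is about 12% of them and 6 about 24%.

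**Step 2: loss unrelated to arm and outcome.** This creates no bias of that kind and costs only power. For n per arm, power = Φ{[√n × 0.25 − 1.96 × √(2 × 0.715 × 0.285)] / √(0.59 × 0.41 + 0.84 × 0.16)}, where 0.715 is the mean of the two rates.

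| Loss in each arm | n per arm | Power |
|---|---|---|
| 0% | 62.0 | 87.9% |
| 5% | 58.9 | 86.2% |
| 10% | 55.8 | 84.2% |
| 20% | 49.6 | 79.7% |

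**Limits of the calculation.** It uses simple proportions at 2 years, whereas the plan estimates locoregional control by Kaplan–Meier. It also treats the removed patients as a fixed number. It shows the order of size and is not a forecast.

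**The case against.** The strongest reply is that 'eligible' here simply means screened and randomised. Patients are screened against Table 2; Table 1 puts the eligibility screen, staging workup and baseline scan before allocation; and the screening section uses the word for that earlier status. The sentence also names its own intent. No section sets up an eligibility re-review, a withdrawal-from-analysis rule or a per-protocol set. And this is a condensed article.

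Much of that stands. It makes the benign reading plausible and suggests that few patients would be affected. It does not settle the wording. In the screening section, eligible patients include those later found normoxic and never randomised, so the word does not describe the randomised set there either. Nor is this a detail merely left to another document: the article states a rule, and the rule as stated disagrees with its label.

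Three stronger readings are tempting, and the documents do not support them:

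- **That the plan departs from intention-to-treat or orders exclusions.** No passage directs the removal of a randomised patient.
- **That patients unable to receive the boost would be dropped as ineligible.** Inability to receive the boost is not a Table 2 criterion, and the sentence already keeps patients in their assigned arm. Criteria fixed at baseline, such as blood counts from the preceding 14 days or p16 status, are also weak candidates for selective re-reading.
- **That Arm 3 control would be inflated by about 3 to 6 percentage points.** With 52 of 62 controlled (83.9%), removing 2 to 4 failures gives 52/60 = 86.7% to 52/58 = 89.7%. That assumes 2 to 4 of only 10 failures are removed, all from Arm 3 and none from Arm 2. It is a one-sided worst case, and small beside the 25-point design difference.

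**Conclusion.** The point holds as a modest bias risk arising from wording. The sentence calls the set intention-to-treat while admitting only eligible patients, and read literally it permits exclusions after an open-label allocation. It is not a demonstrated departure from intention-to-treat.

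The size cannot be derived from the document. It depends on two assumptions: how many randomised patients would be judged ineligible, and how selectively. One selectively dropped failure has almost no effect. It takes about six one-sided removals, roughly a quarter of the expected Arm 3 failures when there is no true effect, to about double the nominal 5% error rate. Whichever meaning the authors intended, the sentence needs changing: if they meant all randomised patients it should say so, and if they meant eligible patients only the label misleads.

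**What to change.** Replace the sentence with one to this effect: all patients randomised to Arm 2 or Arm 3 will be analysed in the arm assigned, regardless of any ineligibility found later and of the treatment received.

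If an eligible-only analysis is wanted, report it as a sensitivity analysis, with eligibility judged only on data from before randomisation and by someone blind to arm.

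The cost is one sentence, or two with the sensitivity analysis. No extra data are needed and the planned 124 patients stay the same. The Trial status section reports recruitment as ongoing at publication; the change should be made before outcomes are compared by arm.
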